### Quantitative data analyses

Characteristics of clinicians, patients and encounters will be summarised using descriptive statistics. We will calculate imaging rates per 100 low back pain patients with 95% confidence intervals and we will determine imaging rates for each primary care profession. We will undertake multilevel logistic regression analysis to determine the effects of clinician- and patient-level factors on inappropriate imaging. Clinician-level factors assessed will include age, sex, profession type, location of clinician training, clinician years in practice, ownership of imaging facilities, knowledge of imaging guidelines, and time spent with patient. Patient-level factors measured at baseline will include age, sex, race/ethnicity, insurance status, living in a metropolitan area, beliefs about usefulness of imaging, education level, duration/severity of low back pain, and three month measurement of satisfaction with treatment and adverse events. Patients consulting each clinician will form a cluster and will be considered as the second level in the multilevel logistic regression. We will also conduct a marginal logistic regression analysis to investigate the effects of clinician- and patient-level factors on inappropriate imaging and estimate the association between inappropriate imaging and explanatory factors in the marginal model using Generalised Estimating Equations. The analysis will allow examination of differences in results from the two models and determine whether the conclusions depend unduly on the model assumptions.

### Methods for study 2

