Patient satisfaction	Single questionnaire item of global perceived effect		X			
Adverse events	Single questionnaire item [79]		X			

^a^Asked as part of STarT Back questionnaire at first visit

**Table 2 Tab2:** Clinician-level factors predictive of inappropriate imaging being investigated, all measured via baseline clinician questionnaire

Factor	Questionnaire items
Age	Single questionnaire item
Sex	Single questionnaire item
Years in practice	Single questionnaire item
Clinician type (family doctor, chiropractor, physiotherapist)	Single questionnaire item
School of entry-to-practice training (for everyone); program of family medicine training (for family doctors only)	Single questionnaire item
Access to imaging (onsite or offsite)	Single questionnaire item asked as part of a list of items about onsite services
Ownership of imaging facilities	Single questionnaire item
Self-identification as having a speciality in back pain	Single questionnaire item [80]
Clinician fear avoidance beliefs	Single questionnaire item: 14 from the Tampa Scale for Kinesiophobia (TSK), modified for clinician [81]
Average time spent with patient	Single questionnaire item
Type of manual technique modalities practiced (for chiropractors)	Single questionnaire item
Beliefs on usefulness of imaging	Single item on questionnaire
Knowledge of imaging guidelines	Single item on questionnaire

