### Encounter data

After each patient consultation during the data collection period, participating clinicians will complete a handwritten 1-page encounter form (see Additional file 1: Appendix 3) for each of 25 consecutive consenting eligible patients with low back pain. There is one type of form for the initial encounter, and another, briefer form, for any follow-up consultations for the same low back pain episode. The encounter form is a modified form previously used in a chiropractic setting to systematically collect clinical data [51]; chiropractors reported that completing the form took 2–3 min per patient. The encounter forms for this project were piloted by two chiropractors, three physiotherapists and two family practitioners, who each recruited between two to five patients with low back pain over a six week period. Only minor changes were made to the form after the pilot study.

At the time of the patient’s initial consultation clinicians will record: key history and clinical findings; working diagnosis; diagnostic imaging ordered/taken; interventions provided or recommended; who is paying for the consultation; and, OHIP number for linkage purposes. Follow up encounter forms will be completed for each visit for up to 6 weeks to determine if any clinical indications for imaging arise. Six weeks was chosen because this is the time when people with low back pain are likely to be recovered, if pain is persisting they have progressed to the sub-acute stage, or if they have a pathological cause this is likely to be definitively diagnosed [57].

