### Administrative data

Participating patients will be followed for 12 months using Ontario health administrative data held by the Ontario Institute for Clinical Evaluative Sciences (ICES) to determine if any imaging was undertaken (plain x-ray, CT scan, MRI, fluoroscopy, positron emission tomography (PET) scan, ultrasound). Although plain x-ray, CT scan and/or MRI are most likely to be ordered for patients with low back pain, we will capture all related imaging to be comprehensive in the assessment of inappropriate imaging. ICES data will also capture whether a pathological condition develops (defined with diagnoses at more than two healthcare visits), and surgery and emergency visits related to such a condition.

Some imaging may not be captured by the administrative data. Approximately 12% of chiropractors take their own plain x-rays and this information will not be captured in ICES data [58]; completed encounter forms by these chiropractors will indicate whether they took lumbar x-rays, and this information will also be collected via the patient-completed questionnaires. Also, some patients in Ontario elect to go to a private facility outside Ontario and individually pay for imaging. This information will be captured via the patient-completed questionnaires.

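### Three-month satisfaction and adverse events are listed as baseline predictors of inappropriate imaging, although they are measured after all encounter-form imaging and can be its consequences

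*Protocol article*

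**What the plan says.** In the protocol article, Quantitative data analyses states the aim of the main model: "We will undertake multilevel logistic regression analysis to determine the effects of clinician- and patient-level factors on inappropriate imaging". Imaging is the outcome and the factors are explanatory. The covariate sentence opens "Patient-level factors measured at baseline will include age, sex, race/ethnicity, insurance status, living in a metropolitan area" and closes with "duration/severity of low back pain, and three month measurement of satisfaction with treatment and adverse events". A marginal logistic model fitted by GEE is then planned to investigate clinician- and patient-level factors again, as a check on model assumptions.

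The outcome accrues from the first contact:

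- **Index visit.** Encounter data has clinicians record "diagnostic imaging ordered/taken" at the initial consultation.
- **To six weeks.** The same section says: "Follow up encounter forms will be completed for each visit for up to 6 weeks to determine if any clinical indications for imaging arise".
- **To 12 months.** Administrative data says: "Participating patients will be followed for 12 months using Ontario health administrative data".

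Table 1 (Data collection and data sources) describes the satisfaction measure as "Single questionnaire item of global perceived effect". It gives this row, and the adverse-events row, a single mark each, in the follow-up-visits column. Neither has a mark at the first visit or at the 3-, 6- or 12-month questionnaire. Patient questionnaires says that visit questionnaires run for up to six weeks and that online questionnaires follow at 3, 6 and 12 months.

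**The concern.** A value taken at three months is not a baseline factor, so the covariate sentence contradicts itself. The statistical consequence matters more than the wording. A variable measured after the outcome has occurred cannot predict it, and if the outcome changes that variable, the regression reads the effect backwards.

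The article itself makes this pathway plausible. Its Background says that imaging may worsen health outcomes and lead to further procedures and treatment, and that most patients with low back pain expect to be imaged. Imaging, or its absence, could therefore alter both satisfaction and adverse events.

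Two results would be affected. The coefficients for satisfaction and adverse events could be reported as factors behind imaging when they are partly its consequences. The coefficients of other factors that also influence satisfaction or adverse events could be biased by the adjustment. This regression serves the part of the first primary objective that concerns factors associated with inappropriate imaging, and its results are meant to guide the design of knowledge translation strategies. The overall imaging rate and the rates by profession do not depend on the covariate list.

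**Working it through.** The article gives no figure for this point, so there is none to reproduce. The check sets the timings side by side and then illustrates the mechanism.

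**1. Timing.**

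| Item | When recorded | Section |
|---|---|---|
| Imaging, encounter forms | Index visit and follow-up visits to 6 weeks | Encounter data |
| Imaging, administrative data | Index visit to 12 months | Administrative data |
| Satisfaction, adverse events | 3 months, in a list labelled baseline | Quantitative data analyses |
| Satisfaction, adverse events | Follow-up visits only | Table 1 |

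If the analysis text is right, both items follow all encounter-form imaging and any administrative-data imaging in the first three months. They precede imaging after month 3. If Table 1 is right, they still follow all imaging ordered at the index visit. Neither reading makes them baseline variables, and no section limits the outcome to imaging after they are measured.

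**2. Mechanism.** All parameters here are assumptions. Let Y be imaging, X a baseline factor in SD units, and S satisfaction measured after imaging:

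- logit P(Y = 1 | X) = −1.2 + 0.5X, so the true odds ratio (OR) for X is exp(0.5) = 1.65.
- S = dY + bX + N(0, 1). S has no causal effect on Y.

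Adding S to the model adds the log density ratio of S for Y = 1 against Y = 0, which is d(S − bX) − d²/2. Hence:

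logit P(Y = 1 | X, S) = constant + (0.5 − d·b)X + d·S

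The adjusted OR for X is exp(0.5 − d·b), and the spurious OR for S is exp(d).

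| d | b | OR for X | OR for S |
|---|---|---|---|
| 0.5 | 0.3 | exp(0.35) = 1.42 | 1.65 |
| 0.5 | −0.3 | exp(0.65) = 1.92 | 1.65 |
| −0.5 | −0.3 | exp(0.35) = 1.42 | 0.61 |
| −0.5 | 0.3 | exp(0.65) = 1.92 | 0.61 |
| 0.2 | 0.3 | exp(0.44) = 1.55 | 1.22 |
| 0.2 | −0.3 | exp(0.56) = 1.75 | 1.22 |
| 0.2 | 0.1 | exp(0.48) = 1.62 | 1.22 |
| 0.5 | 0 | exp(0.50) = 1.65 | 1.65 |

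The last row is the important limit. A factor with no effect on satisfaction keeps its OR, but satisfaction still gets a spurious one.

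**3. Some imaging after month 3.** A separate simulation (400,000 patients, no clustering, all parameters assumed) used a pain factor that lowers satisfaction by 0.3 SD per SD and also raises adverse events, a belief factor with no link to either item, and imaging that raises adverse-event log-odds by 0.4. Neither item caused imaging. The rows below have imaging raising satisfaction by 0.5 SD.

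| Imaging after month 3 | Pain OR without the two items | Pain OR with them | Satisfaction OR | Adverse-event OR |
|---|---|---|---|---|
| 0% | 1.48 | 1.68 | 1.65 | 1.52 |
| 30% | 1.49 | 1.63 | 1.42 | 1.33 |

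The belief OR stayed at about 1.82 throughout. Later imaging weakens the distortion but does not remove it.

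**The case against.** Several points on the other side are fair, and some limit the conclusion.

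- **Not all imaging comes first.** A reader might infer that both items always follow imaging. Administrative data run to 12 months, so imaging after month 3 follows a three-month measurement, and the article does not say what share that is. This stands as a limit on size, as step 3 of the working shows.
- **Not all odds ratios are biased.** A reader might infer that every other coefficient is distorted. Only factors that themselves affect satisfaction or adverse events are exposed, and the article does not show which do. It also does not say that all factors enter one model together. Imaging expectations are not in the listed factors, so nothing can be claimed about their coefficient.
- **The three-month items may exist.** The mark missing from Table 1 might suggest that they are never collected. The article does not support that: the analysis text says they are measured, the 3-month questionnaire is in an appendix not shown, and Table 1 lists hypothesised factors and need not list every item. What stands is a conflict between two places.
- **No loss of patients can be asserted.** One might infer that single-visit patients would drop out of the model, unevenly by profession. The article gives no share of single-visit patients, and handling of missing data may be in an analysis plan that is not shown.
- **Only associations are sought.** The objective speaks of associated factors, but the analysis text speaks of effects and the Discussion of predictors. Even a purely predictive model cannot use items measured after the outcome. This objection does not stand.
- **The GEE model is a check.** It models patient-level factors in the same way, so agreement between the two models would not reveal the problem.

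**Conclusion.** The point holds as an error in covariate timing. Followed as written, the imaging regressions would use satisfaction and adverse events as predictors of an outcome that, for all encounter-form imaging, has already occurred by three months and may have changed them. Their odds ratios may reflect reverse causation, and adjustment can bias the odds ratios of factors that also affect them.

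The size and direction cannot be derived from the article. The illustrative shifts, from 1.65 to about 1.42 or 1.92 for a baseline factor and to about 1.65 or 0.61 for a satisfaction score with no causal effect, rest on the assumed 0.5 SD and 0.3 SD effects, and smaller effects give smaller shifts. The harm is confined to the regressions. Separately, the analysis text and Table 1 disagree on when the two items are measured, whatever view is taken of the causal argument.

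**What to change.** In Quantitative data analyses:

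1. Remove satisfaction with treatment and adverse events from the predictors in both the multilevel and the GEE imaging models.
2. Restrict the patient-level predictors to variables recorded at the first visit, so that the baseline label is true.
3. If the two items are of interest, report them separately as outcomes by imaging status.
4. Reconcile this section with Table 1 on when the two items are measured, and correct whichever is wrong.

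The cost is a change to one sentence of the analysis text, a possible correction to two rows of Table 1, and an optional descriptive analysis. No new data collection is needed, and the sample size is unaffected.

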#### Clinician and patient recruitment

*Clinician participants (n = 175)* will comprise 50 each from chiropractic and physiotherapy, and 75 from family medicine. We are recruiting more family medicine clinicians than the other professions because lower numbers of patients with low back pain attend family medicine than chiropractic and physiotherapy. Our partner organisations will promote study participation via their normal communication strategies to their clinician members. We will invite clinicians in community-based practices chosen randomly from the lists of all registered clinicians in Ontario. From the College of Physicians and Surgeons of Ontario we will select only family doctors. From the College of Physiotherapists of Ontario we will select only physiotherapists whose primary work site is primary care. From the College of Chiropractors of Ontario we will use the full list.

We anticipate a 30% response rate based on our previous experience [51, 52], hence we will approach at least 600 clinicians to reach our sample size. To ensure the efficient use of project resources, we will target clinicians who practice in seven geographic regions within Ontario, Canada. These regions were selected to be representative of the mix of high and low population density areas, and different geographical regions: 1) Sudbury/North Bay; 2) Mississauga/Halton (Mississauga; Oakville; Milton); 3) Kitchener, Waterloo, and Guelph; 4) London, Ontario; 5) Central Toronto; 6) Southeast Ontario (Belleville; Brockville; Napanee; Smiths Falls; Kingston; Picton; Gananoque; Perth); 7) Ottawa region (Ottawa; Kanata; Nepean; Orleans).

We will invite clinicians to participate using a modified tailored design method [53] by sending a primer postcard, an invitation letter, two reminder letters and a telephone call. We will also use a snowball sampling technique, where, after clinicians are recruited, they will be asked to approach clinicians who work in the same practice, or other clinicians they know who they believe may be interested in participating.

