Recruited clinicians will complete a baseline demographic questionnaire including: sex; age; training location; years in practice; and proximity of practice to imaging facility (see Additional file 1: Appendix 1 for questionnaire). Results of this questionnaire will be used to assess clinician representativeness by comparing to available province-wide clinician demographic characteristics and also be used as clinician-related factors when modeling inappropriate use of imaging.

*Patient participants (n = 3750):* Consecutive patients with low back pain will be invited to participate until up to 25 are recruited from each participating clinician. Research staff will visit each participating practice to train the practice staff and clinicians in the study procedures. To reduce possible selection bias, we will encourage practice staff at each location to follow a strategy suitable for their practice that maximises the chances of recruiting consecutive patients with low back pain. For clinicians in solo practice without reception staff, typical of some chiropractors and physiotherapists, clinicians will approach potential participants directly. For clinicians in circumstances where practice reception staff are likely to know in advance that a patient’s consultation is for low back pain, practice reception staff will be asked to inform every such patient about the study during the recruitment period and provide them with recruitment information to read in the waiting room. If the patient consents to participate, the practice staff will inform the clinician, who will then complete the enrolment process, including screening for participation.

We are allowing 12 months for patient recruitment; that is, approximately two patients with low back pain recruited per month per clinician, which is feasible based on incidence rates of low back pain presentations in these settings [4, 54, 55]. Practices will be offered reimbursement for staff time required to recruit patients and collect data.

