### Data access plan

ICES, funded by the Ontario Ministry of Health and Long Term Care, links encoded population-based health information at the patient level. The practice-level and patient questionnaire data collected by the study team will be migrated to ICES for linkage. Analysis will be conducted using the following ICES datasets: OHIP database for imaging fee codes; OHIP Claims Database; National Ambulatory Care Reporting System Database for emergency room visits; Canadian Institute for Health Information Database for hospitalisation and surgery; Ontario Cancer Registry.

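### Snowball recruitment adds same-practice colleagues, but the multilevel model stops at the clinician, so standard errors can be too small for practice-shared factors and for rates

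*Protocol article*

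**What the plan says.** Under Clinician and patient recruitment, clinicians are invited at random from the professional registers. A snowball step follows: once recruited, "they will be asked to approach clinicians who work in the same practice, or other clinicians they know". No limit or expected number of clinicians per practice is given. The same section notes that some clinicians work alone: "For clinicians in solo practice without reception staff, typical of some chiropractors and physiotherapists".

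Under Quantitative data analyses, the hierarchy is described in one sentence: "Patients consulting each clinician will form a cluster and will be considered as the second level in the multilevel logistic regression". A marginal model follows, which estimates the association between inappropriate imaging and the "explanatory factors in the marginal model using Generalised Estimating Equations". Its clustering unit is not stated. The clinician factors listed there are age, sex, profession, training location and years in practice, then "ownership of imaging facilities, knowledge of imaging guidelines, and time spent with patient". Table 2 adds an entry that begins "Access to imaging (onsite or offsite".

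The Sample size justification uses a single ICC of 0.088 with 25 patients per cluster and has no practice component. The Data access plan shows that practice-level data are held: "The practice-level and patient questionnaire data collected by the study team will be migrated to ICES for linkage".

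**The concern.** The snowball step can place two or more clinicians from one practice in the sample by design. Colleagues at one site are likely to share equipment, local habits and patient mix. The study adds a further source of dependence: staff are trained practice by practice, and each location follows a recruitment strategy suited to it. A model with only patient and clinician levels treats these colleagues as independent of one another.

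The rate of inappropriate imaging and the factors associated with it form the first primary objective, and the results are meant to shape knowledge translation strategies. If intervals for practice-shared factors or for the rates are too narrow, a strategy could be aimed at a factor whose association is noise. The planned comparison of the multilevel and marginal models is meant to show whether conclusions depend on model assumptions. If both use the clinician as the cluster, they share the omission and may agree for that reason.

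**Working it through.** **The plan's own figure.** The only clustering calculation in the article is the power statement: at least 95% power for a 6-point difference between professions. With 3750/3 = 1250 patients per profession and a design effect of 1 + (25 − 1) × 0.088 = 3.112, the effective size is 1250/3.112 ≈ 402 per group. Power (two-sided 5%, assumed) is then 0.72 for 10% v 16% and 0.41 for 39% v 45%. The stated figure is not reproduced from these inputs. That is a separate matter, and the present point does not rest on it. The design effect of 3.112 is what the clinician-only analysis implies, and it is the baseline below.

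**Inputs from the article.** ICC 0.088 and m = 25 patients per clinician (Sample size justification).

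**Inputs assumed, because the article does not give them.** K, the number of participating clinicians per practice; and ρ, the practice-level correlation, taken as 10%, 25% or 50% of the 0.088 (0.0088, 0.022, 0.044). The total ICC stays at 0.088.

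**Factor shared by the whole practice, or an overall rate.**

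True design effect = 3.112 + 25 × (K − 1) × ρ. The ratio of true to clinician-only standard error is √(true design effect / 3.112). Actual type I error at nominal 5% is 2 × [1 − Φ(1.96 / ratio)].

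| K | ρ | True design effect | SE ratio | Type I error |
|---|---|---|---|---|
| 1 | any | 3.112 | 1.00 | 5.0% |
| 2 | 0.0088 | 3.332 | 1.04 | 5.8% |
| 2 | 0.022 | 3.662 | 1.08 | 7.1% |
| 2 | 0.044 | 4.212 | 1.16 | 9.2% |
| 3 | 0.0088 | 3.552 | 1.07 | 6.7% |
| 3 | 0.022 | 4.212 | 1.16 | 9.2% |
| 3 | 0.044 | 5.312 | 1.31 | 13.4% |

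A ratio of 1.16 means that the model's standard error is 1 − 1/1.16 = 14% below the true one; a ratio of 1.31 means 24% below.

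**Mostly single-clinician practices.** If a fraction q of clinicians is paired with one colleague and the rest are alone, the added term is 25 × q × ρ. With q = 0.2 and ρ = 0.0088 the design effect is 3.112 + 0.044 = 3.156, ratio 1.01, type I error 5.2%. With q = 0.3 and ρ = 0.044 it is 3.112 + 0.33 = 3.442, ratio 1.05, type I error 6.2%.

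**Factor balanced within practice.** True design effect = 3.112 − 25 × ρ, that is 2.892, 2.562 and 2.012, with ratios 0.96, 0.91 and 0.80. Here the clinician-only standard error is too large.

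**Check by simulation** (150 clinicians with 25 patients each, logistic model, sandwich variance by clinician, 1500 runs per setting):

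- Practice-constant factor: ratio 1.08 (K = 2, 25% share), 1.15 (K = 2, 50%) and 1.31 (K = 3, 50%), with type I error 7.7%, 8.9% and 13.3%.
- Factor unrelated to practice: ratio 1.01–1.02, type I error 5.5–5.6%.
- Factor varying within practice: ratio 0.84–0.94, type I error 1.9–3.2%.

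The simulation agrees closely with the formula.

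**The case against.** **Scope.** A reader might infer that standard errors for all clinician factors are too small. The article does not support that. Most of the listed factors (age, sex, training location, years in practice, guideline knowledge) are personal attributes. If they are unrelated to practice the clinician-only standard errors are about right, and if they vary mainly within practice they are too large. This objection stands and limits the point to practice-shared factors and rates.

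**Which factors are shared.** Access and ownership are recorded by clinician questionnaire, and ownership could differ between a principal and an associate at one site. Onsite access is in Table 2 but not in the list of model factors in the analysis section. This stands in part: access is usually common to a site and ownership often is, but the article does not establish either. That list is introduced as what the factors will include, so it need not be complete.

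**Size.** Random invitation is the main route, snowballing also reaches outside contacts, and some clinicians are solo. This stands: the upper figures need two or three participating clinicians in every practice.

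**Omission or condensed reporting.** A reader might also infer that both models certainly cluster on clinician alone. The text does not say so: the GEE unit is unstated, and calling the clinician the second level does not strictly rule out a third. Such detail is often left to an analysis plan. The point survives because the article does state a hierarchy, that hierarchy does not match the recruitment it describes, and the clinician is the only cluster it defines.

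**Conclusion.** The stated multilevel analysis does not match the stated recruitment. The conclusion is conditional: where practices contribute more than one clinician and practice-level correlation exceeds zero, clinician-only standard errors are too small for factors colleagues share (onsite access, often ownership, and profession where a practice has a single profession) and for imaging rates whose intervals use clinician clusters.

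The omission is clear from the text, but its size is not. The range runs from almost no effect, if most practices supply one clinician, to a type I error of about 13% with three clinicians in every practice and half of the ICC at practice level. These figures rest on the assumed K and ρ, on equal cluster sizes, and on the 0.088 being the total clinician-level ICC. The change is worth making because standard errors are wrong in one direction or the other for any factor tied to practice, and the correction is cheap.

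**What to change.** - Record a practice identifier and the recruitment route (random invitation or snowball) for each clinician.
- Add a practice-level random intercept, so that patients are nested in clinicians and clinicians in practices.
- State the GEE clustering unit and set the robust variance to cluster on practice. Use the same unit for the confidence intervals of the imaging rates.
- Report the distribution of clinicians per practice and the estimated practice variance, so that readers can see whether the level mattered.

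The cost is small. Research staff visit every participating practice and practice-level data already go to ICES, so the identifier should be easy to obtain. The model gains one variance term, and intervals for practice-shared factors become slightly wider. If the practice variance is near zero, or nearly all practices supply one clinician, results will hardly change. In that case the practice variance may be poorly estimated, and the practice-clustered GEE can carry the check.
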